## Abstract

**Background:**

The rapid increase in the number of elderly family caregivers underlines the need for new support systems. Internet-delivered psychological interventions are a potential approach, as they are easy to access for family caregivers who are often homebound with their care recipient. This study examines the relative effectiveness of an internet-based acceptance and commitment therapy (ACT) intervention or a standardized institutional rehabilitation program, first, in reducing depressive symptoms, and second, in improving the well-being and quality of life of elderly family caregivers compared to a control group receiving support from voluntary family caregiver associations.

**Methods:**

156 family caregivers aged 60 or more are studied in a quasi-experimental study design that compares three groups of family caregivers (Group 1; *n* = 65: a guided 12-week web-based intervention; Group 2, *n* = 52: a standardized institutional rehabilitation program in a rehabilitation center; Group 3, *n* = 39: support provided by voluntary caregiver associations). Data collection is performed at three time-points: pre-measurement and at 4 months and 10 months thereafter. Caregivers’ depressive symptoms as a primary outcome, and perceived burden, anxiety, quality of life, sense of coherence, psychological flexibility, thought suppression, and personality as secondary outcomes are measured using validated self-report questionnaires. Physical performance and user experiences are also investigated. Between-group differences in the effects of the interventions are examined using multiple-group modeling techniques, and effect-size calculations.

**Discussion:**

The study will compare the effectiveness of a novel web-based program in reducing depressive symptoms and improving the psychological well-being of elderly family caregivers, or a standardized institutional rehabilitation program representing usual care and a control group receiving support offered by voluntary caregiver associations. The results will expand the knowledge base of clinicians and provide evidence on effective strategies to improve the mental health and overall quality of life of elderly family caregivers.

**Trial registration:**

The study was retrospectively registered in www.clinicaltrials.gov (ClinicalTrials.gov Identifier: NCT03391596 on January 4, 2018.

## Background

An aging population requires the provision of both formal and informal long-term care [1, 2]. Formal care refers to health and social care provided by professionals and informal care to care given by a family member on a voluntary basis [2]. Informal care is especially of important from the economic standpoint and hence sustainability of the health care system [3, 4]. Family caregivers play an essential role in providing spouses and close ones, among others, with daily care and assistance [4]. However, providing care can have a negative effect on the caregivers’ physical and psychological health. Spousal caregivers are particularly vulnerable as they often live with their care recipient, and often face chronic health challenges of their own. Many have depressive symptoms [5]. Caregiving may also be highly rewarding emotionally [6]. Nevertheless, despite its positive aspects, the negative impact on caregivers and how this might be ameliorated merit further investigation [5].

Most of the previous traditional interventions on family caregivers’ psychological, physical and social wellbeing have addressed the caregivers of care recipients with dementia [7]. Individual and family counseling, psychoeducational programs, skills training programs and multi-component intervention programs have shown potential in improving caregiver mood, quality of life and delaying institutionalization of the care recipient [7–9]. Technology-driven programs, delivered via, e.g. phones, smart phone applications, videoconferencing and the internet are a rapidly expanding means of supporting family caregivers at lower costs and with improved accessibility [5, 10, 11]. Preliminary data suggest that internet-based interventions can reduce depression and caregiver burden and enhance quality of life similar to the same extent as traditionally delivered interventions [5, 10–12].

Acceptance and Commitment Therapy (ACT) is a relatively new form of cognitive behavioral therapy [13]. Its core message is: accept what is out of your personal control, and commit to actions that improve and enrich your well-being and life. ACT focuses on increasing psychological flexibility through acceptance, mindfulness and value processes [14]. Several meta-analyses support its effectiveness across a range of psychological problems [15–17]. A randomized trial that investigated ACT versus cognitive-behavioral therapy (CBT) for family caregivers of patients with dementia found ACT to be as beneficial as CBT [18]. Further studies are required to confirm the effectiveness of ACT-based interventions among elderly caregivers. To the best of our knowledge, no trials thus far have investigated the effectiveness of web-based ACT interventions in enhancing the well-being of elderly family caregivers.

## Aim and main hypotheses

The study aim is to investigate the relative effectiveness of 1) a guided Acceptance and Commitment Therapy (ACT) -based online psychological intervention and 2) a standard rehabilitation provided by rehabilitation centers in, first, reducing depressive symptoms, and second, in improving well-being and quality of life of elderly family caregivers, compared to 3) an active control group receiving support from voluntary family caregiver organizations. The study is thus a quasi-experimental trial comparing three groups of caregivers (Group 1; *n* = 65: guided 12-week web-based intervention; Group 2, *n* = 52: standardized rehabilitation program in a rehabilitation center; Group 3, *n* = 39: support given by voluntary family caregiver organizations). The same measurements will be conducted in all three groups, and between group differences in changes, primarily in depressive symptoms, but also, in experienced burden, anxiety, quality of life, sense of coherence, psychological flexibility, thought suppression, and personality will be studied using self-report questionnaires at pre-measurement, and at 4 and 10 months thereafter. Physical performance at pre-measurement will also be investigated. In our controlled trial, we hypothesize that the guided web-based ACT intervention will be equally effective in alleviating depressive symptoms and perceived burden and in improving mental well-being and quality of life as the standardized rehabilitation program but superior to support provided by voluntary family caregiver organizations. In addition to the aforementioned controlled trial, we aim to identify demographics and psychological variables (age, gender, personality, depressive mood, experienced burden, quality of life, sense of coherence, psychological flexibility, and suppression of thoughts) that could predict change over time (at pre-measurement, at four and 10 months thereafter). A further aim is to examine potential mediators, including psychological flexibility and suppression of thoughts, on the effects of the interventions Moreover, we aim to study user experiences and satisfaction with the web-based program, that is, how family caregivers experience and accept the web-based ACT intervention.

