### Statistical analysis

The sample size for the trial was estimated based on the change in depressive symptoms (the primary outcome) measured by the BDI-II in a previous study [40]. A sample size of 50 elderly family caregivers in each of 1) an Acceptance and commitment therapy –based online psychological intervention group (experimental group), and 2) a standardized institutional caregiver rehabilitation program (active comparison group representing usual care), and 3) an active control group receiving support from a caregiver associations receiving support provided by voluntary caregiver associations was calculated as the minimum required to detect a 5.8 point decrease in BDI-II in 1) the ACT intervention group or 2) the standardized institutional caregiver rehabilitation program vs. no change in 3) the caregiver support group at the 10-month post-measurement to achieve 80% power. The calculations were based on a one-sided General Estimation equation (GEE) model [41] using the pre-measurement, four-month and 10-month post-intervention measurements. We assumed that the post-measurement difference between the 1) intervention or 2) usual care group vs. 3) caregiver support group would be 5.8 points (*SD* = 4.8) lower than at pre-measurement (9.3 points, *SD* = 7.8). Thus, assuming an attrition rate of 20%, a sample size of 123 (41 per group) was expected. Hence the target sample size was 150 participants, with 50 in each group.

Statistical analyses will be conducted using Mplus (version 7) [42] and SPSS IBM version 24. Analyses will be performed on all participants. Baseline differences between the groups will be examined by using t-tests and chi-square -tests. Data will be analyzed using the IBM SPSS statistics version 22.0 or newer and Mplus statistical package 7.1. Analyses will be controlled for possible baseline differences between the groups. Between group differences in the stability of the outcome measures will be examined using multiple-group modeling techniques. Full information maximum likelihood (FIML) estimation on the assumption of data missing at random (MAR) will be used in analyzing incomplete data. When the normality assumption is violated, maximum likelihood with robust standard errors (MLR) will be used. The level of significance will be set at 0.05. Cohen’s *d* will be used to estimate effect sizes, and to reflect the clinical significance of the interventions.

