## Discussion

### The aim of the study

This article describes a research protocol for a quasi-experimental trial investigating whether a guided web-based acceptance and commitment therapy (ACT) intervention (Group 1) or a standardized rehabilitation program provided by rehabilitation centers (Group 2) is more effective in reducing depressive symptoms and improving the well-being and quality of life of elderly family caregivers, compared to support provided by voluntary family caregiver associations (Group 3). A further aim is to investigate whether personality, psychological flexibility or other psychological variables predict, or mediate the effects of the web-based ACT intervention. User experiences and the satisfaction of family caregivers with the web-based intervention will also be examined. We expect the effect of the web-based intervention to be equal to the effect of the established comparator group (Group 2), and show more positive effects on depressive symptoms and well-being than the support provided by family caregiver associations (Group 3).

Family caregivers who provide complex chronic care play a crucial role in the long-term care of older adults worldwide. Several studies have shown, however, that while caring for a person with a long-term condition or disability may be rewarding, it may also have serious negative effects on the caregivers’ physical and mental health [43, 44]. Depression, stress and other types of psychological distress are major health concerns among family caregivers [5]. It is, therefore, of great importance to help to decrease the negative impact of caregiving on family caregivers. Low intensity interventions combined with technology enable 24/7 committed and stressed caregivers to participate when they have both the time and need to do so. However, it is important to evaluate the acceptability of technology-based interventions and their effects on psychological and physiological variables.

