This study will provide knowledge on the effectiveness and acceptability of a web-based intervention aimed at decreasing depressive symptoms and increasing well-being and quality of life among caregivers aged 60 or more. We compare a web-based intervention with a standardized institutional rehabilitation and support provided by family caregiver associations. While the current institutional rehabilitation program has successfully met the caregivers’ physical needs, results show that it has not improved caregivers’ mental health [45]. If the web-based CareACT intervention improves family caregivers’ mental health and if their physical functioning is also found to be on an acceptable level for independent living, the web-based intervention should be made available to all family caregivers. If support received from family caregiver associations does not show changes comparable with those of the web- and institutional programs in reducing depressive symptoms, it may nevertheless offer a potential environment for implementation of the CareACT program which has proven effectiveness. In sum, this study will increase our understanding of the effectiveness and suitability of acceptance, mindfulness and value-based brief interventions for elderly family caregivers suffering from depressive symptoms and psychological distress.

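### Web ACT is hypothesised to equal rehabilitation, but the plan sizes and analyses only for differences, with no margin or interval rule, and its statements about rehabilitation's effect conflict

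*Protocol article*

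**What the plan says.** Under Aim and main hypotheses, the protocol article states one joint hypothesis: "the guided web-based ACT intervention will be equally effective in alleviating depressive symptoms and perceived burden" as the standardised rehabilitation programme, "but superior to support provided by voluntary family caregiver organizations". The Discussion (The aim of the study) repeats the first half: "We expect the effect of the web-based intervention to be equal to the effect of the established comparator group (Group 2").

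The sample-size text under Statistical analysis covers a different contrast. Fifty per group is the "minimum required to detect a 5.8 point decrease in BDI-II" in the ACT group or the rehabilitation group "vs. no change in 3) the caregiver support group at the 10-month post-measurement to achieve 80% power", from a one-sided GEE calculation. The assumed difference is "5.8 points (*SD* = 4.8) lower than at pre-measurement (9.3 points, *SD* = 7.8"). On analysis the section says: "Between group differences in the stability of the outcome measures will be examined using multiple-group modeling techniques". The significance level is 0.05, and Cohen's d is the effect size. No margin, equivalence or non-inferiority test, or confidence-interval criterion is given for Group 1 against Group 2.

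On the comparator, the Discussion credits the institutional programme with meeting caregivers' physical needs, but adds that "results show that it has not improved caregivers’ mental health".

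**The concern.** A hypothesis of equal effect needs a statement of how small a difference counts as equal, and a rule that the data must exclude anything larger. A test for a difference supplies neither. When it is non-significant, the two programmes may be close, or the comparison may be too imprecise to separate them. ACT could beat Group 3, show no significant difference from Group 2, and be reported as equal to rehabilitation while the data remain compatible with a material deficit.

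The second strand concerns the comparator. The sample-size text gives rehabilitation the same BDI-II benefit as ACT, and the Discussion calls it established. The same Discussion then reports that it has not improved mental health. If that report carries over to depressive symptoms, parity with rehabilitation is not evidence of benefit. ACT could then be both equal to Group 2 and superior to Group 3 only if Group 2 also outperformed Group 3, and no such condition is set.

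The Limitations section says the results are meant to help policy-makers develop rehabilitation strategies, so the wording of this claim matters.

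**Working it through.** **The plan's own figure.** The plan states 41 evaluable per group for a 5.8-point difference, one-sided, 80% power. Taking alpha 0.05, n = 2 × [SD × (1.645 + 0.842) / 5.8]². This gives 8.5, so 9, at SD 4.8 and 22.4, so 23, at SD 7.8. Two-sided (1.96 in place of 1.645) it gives 11 and 29. The stated inputs do not reach 41. A change-score version with SD 7.8 × √[2(1 − ρ)] gives 45 at ρ = 0 and 36 at ρ = 0.2, so an unstated low correlation could produce 41. The figure is not reproducible from the text, but it is not shown to be wrong. It concerns only the comparison with Group 3; no figure is stated for Group 1 against Group 2.

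**Inputs for Group 1 against Group 2.** Recruited: 65 and 52 (Aim and main hypotheses). Attrition: 20% (Statistical analysis). Completers: 65 × 0.8 = 52 and 52 × 0.8 = 41.6, taken as 42. SD: 4.8 and 7.8, the two stated values, used as a range. Assumed here: a simple two-group comparison, normal approximation, and no gain from repeated measures or baseline adjustment.

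**Precision.** SE = SD × √(1/52 + 1/42) = SD × 0.2075.

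- SD 4.8: SE = 0.996; 95% half-width = 1.96 × 0.996 = 1.95 points.
- SD 7.8: SE = 1.618; 95% half-width = 1.96 × 1.618 = 3.17 points.

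**Chance that a real deficit goes undetected.** P(non-significant) = Φ(1.96 − δ/SE) − Φ(−1.96 − δ/SE).

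**Equivalence power when the true difference is zero.** With two one-sided 0.05 tests (90% CI inside ±m), power = max[0, 2Φ(m/SE − 1.645) − 1].

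The protocol gives no margin, so half the planned effect serves as an illustrative value for both δ and m. The sample-size wording most directly makes the effect 5.8, so half is 2.9. If 5.8 is instead read as the post-treatment mean, the effect is 9.3 − 5.8 = 3.5 and half is 1.75.

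| δ = m | SD | δ/SE | P(non-significant) | Equivalence power |
|---|---|---|---|---|
| 2.9 | 4.8 | 2.91 | 17% | 79% |
| 2.9 | 7.8 | 1.79 | 57% | 12% |
| 1.75 | 4.8 | 1.76 | 58% | 9% |
| 1.75 | 7.8 | 1.08 | 81% | 0% |

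**The comparator statements side by side.** Statistical analysis assumes that Group 2 falls by as much as Group 1 on the BDI-II while Group 3 does not change. The Discussion calls Group 2 established, yet reports no improvement in mental health under the programme it represents. The protocol does not explain how these fit together.

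**The case against.** Five objections deserve an answer.

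- **The decision rule is inferred.** A reader might infer that the plan will treat a non-significant Group 1 against Group 2 result as confirming equality. No sentence says so: differences are to be examined, with Cohen's d. This stands. The point is that the stated analysis offers no other route to the hypothesis.
- **Equality is not the lead claim.** It is one half of a joint hypothesis, and the sample size serves the other half. Requiring superiority over Group 3 also guards against two ineffective programmes being declared a success. This stands too, but that safeguard does not make the claim of equality with Group 2 testable.
- **The sample may suffice.** A reader might infer that equivalence was hopeless from the outset. That needs the 1.75-point margin, which rests on the less direct reading of 5.8. At 2.9 points and SD 4.8, power is 79%, and repeated measures could improve precision. Adequacy therefore turns on a margin that is not stated.
- **The report on mental health is limited.** It rests on a cited source that is not at hand, and it does not mention the BDI-II. It does not establish that rehabilitation has no effect on the primary outcome. It does conflict with the assumed benefit, and that needs an explanation.
- **A margin could sit in an unseen analysis plan.** Detail may. But the article itself states the hypothesis, the contrast it is sized for and the form of analysis, and these do not match.

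**Conclusion.** The point holds in this form: the analysis as described cannot support the equality half of the hypothesis, and the statements about rehabilitation's effect conflict.

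The size depends on assumptions. Under those set out above, the 95% CI for Group 1 minus Group 2 extends about 2 to 3 points either side of the estimate. That interval may be tight or loose enough depending on a margin the protocol never fixes. Requiring the 95% rather than the 90% CI to lie inside the margin would lower the equivalence powers further.

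This should be corrected, but it does not undermine the comparisons with Group 3. Allocation is not randomised, which limits any comparison of Groups 1 and 2 whichever way it is framed.

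**What to change.** 1. Keep the superiority comparisons of Group 1 with Group 3 and of Group 2 with Group 3, as sized. Neither needs to be dropped.
2. Report Group 1 against Group 2 as an estimated difference in BDI-II change with its 95% CI, and state that a non-significant difference will not be read as equal effectiveness. Reword the hypothesis and the matching Discussion sentence accordingly.
3. If the equality claim is kept, fix and justify a BDI-II margin before the 10-month data are analysed. Name the confidence level, and require the interval to lie wholly inside the margin. Interpret equality as benefit only if Group 2 is itself better than Group 3.
4. Reconcile the Discussion's report on rehabilitation and mental health with the Group 2 benefit assumed in the sample-size text and with the description of Group 2 as established.

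The cost is redrafting the hypothesis, analysis and Discussion text. No new data are needed. The sponsor may have to give up the claim of equality.

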## Methods/design

### Study design

This study is a quasi-experimental controlled trial comparing three groups of caregivers. Group 1 is an experimental group receiving an ACT-based, guided internet intervention. Group 2 is an active comparator group receiving a standardized rehabilitation program in the rehabilitation center (usual care). Group 3 is a control group receiving support given by voluntary family caregiver associations. Data will be collected at three time points; pre-measurement, and at four and 10 months thereafter. Outcome measures are depressive symptoms (the primary outcome), caregivers’ burden, anxiety, quality of life, sense of coherence, personality, psychological flexibility, suppression of thoughts, and physical performance. We are also interested in user experiences of the novel web-based intervention. The study design with intervention arms is shown in detail in the flow chart presented in Fig. 1.

**Fig. 1 Fig1:**
[figure not shown]
Flow chart of the study design

The protocol follows the Standard Protocol Items: Recommendations for Interventional Trials (SPIRIT) 2013 statement.

Data are collected from three Finnish rehabilitation centers and five voluntary family caregiver associations. The study has been approved by the ethics committee of the Central Finland Health Care District (Approval Number 3E/2016), and registered with ClinicalTrials.gov with the identifier NCT03391596. The study and data is conducted in phases to improve the flow of the trial. The first phase of the web-based ACT intervention group (Group 1) started in January 2017 in the city of Jyväskylä, and the second phase in September 2017 in the city of Tampere. The study includes pre-measurements before the interventions, measurements 4 months after the pre-measurements, and post-measurements 10 months after the pre-measurements. Pre-measurements for all groups were carried out between January and December 2017. The last post-measurements will be collected in October 2018.

### Study population

A total of 156 family caregivers (Fig. 1) aged 60 years or over reporting caregiving burden and/or depressive symptoms were recruited.

### Procedure for recruitment

The experimental group (Group 1) was recruited using advertisements in local newspapers. Interested participants were requested to call or email the members of the research team at the GeroCenter Foundation. Potential participants were informed by phone about the study and, those willing to participate, asked to give their verbal informed consent after which they were screened to ensure they met the basic inclusion criteria. After this initial screening, a structured interview was performed to check the eligibility criteria in detail.

Inclusion criteria for the experimental group (Group 1) were 1) at least 60 years of age, 2) perceived depressive symptoms and/or psychological distress, and 3) the possibility to use a computer with internet connection or willingness to use a tablet provided by the study. The exclusion criteria included 1) diagnosed severe mental disorder and 2) parallel psychological treatment. Screening for distress and/or depressive symptoms was implemented by telephone using four questions based on the DEPS screening instrument [19]. The questions were: During the last 4 weeks, how much have you been bothered by any of the following problems: 1) Have you suffered from sleeping difficulties? 2) Have you been bothered by feeling down, depressed? 3) Have you been bothered by feeling tired, or having little energy? and 4) Have you been bothered by thoughts that all the joy has gone from your life? The caregiver was included in the study if scored at least 1 point on the 4-point response scale for each question. The response scale was as follows: Not at all (0 points), To some extent (1 point), Quite a lot (2 points), Very much (3 points). Participants who passed the screening were assigned to the intervention group (Group 1).

Participants in Group 2 and 3 were recruited by contacting rehabilitation centers and voluntary family caregiver associations by email. We asked if it would be possible for members of the research group to meet potential participants at these centers/associations to inform them about the study. To be eligible for participation, family caregivers had to meet the inclusion criteria, but none of the exclusion criteria. The inclusion criteria were 1) at least 60 years of age, 2) symptoms of psychological distress and burden as determined by a physician’s examination (Group 2) and self-report (Group 3). The exclusion criteria were the same as for Group 1. Participation in the study was voluntary. A written and signed informed consent was obtained from all participants before the start of the pre-measurements.

